## Abstract

**Background:**

Excessive gestational weight gain can result in poor maternal and child health outcomes. Estimates from single studies indicate the prevalence of excessive gestational weight gain in Australia could lie between 38 and 67 %. The risk of excessive weight gain can be reduced through healthy eating and exercise. We describe the rationale and methods of the Get Healthy in Pregnancy Service, a trial service which aims to support women in achieving appropriate gestational weight gain through an existing telephone-based health coaching service.

**Methods/Design:**

This study aims to compare the effectiveness of a telephone-based health coaching program versus provision of information only in supporting pregnant women to achieve appropriate gestational weight gain. A pragmatic stratified clustered randomised controlled trial will be conducted with 710 women who present to 5 hospitals for their first antenatal appointment during the recruitment period (6–8 months), have a pre-pregnancy body mass index (BMI) ≥ 18.50 (healthy weight or above), are 18 years and over, singleton gestation, English speaking, have no pre-existing medical conditions that may limit their ability to exercise or require a restricted diet and are 18 weeks or less gestation. Hospitals will be randomised into one of two intervention models: a) information only; or b) information plus 10 telephone-based health coaching sessions with a university qualified coach. Both interventions will set a weight-range target with pregnant women. The women attending antenatal clinics at participating hospitals will be screened at their initial hospital appointment to assess their eligibility. Women recruited to the trial will have a number of measures recorded including anthropometrics (self-reported height and weight) and dietary and physical activity scores during and following pregnancy. These measurements will be collected at baseline (prior to 18 weeks gestation), 36 weeks gestation and 12 months post-birth.

**Discussion:**

This study responds to a need for an effective intervention that targets excessive gestational weight gain at a population level. This study investigates the potential for an innovative intervention combining two existing services; a free state-wide telephone-based health coaching service and hospital-based antenatal care to support pregnant women to achieve healthy weight gain during pregnancy. The use of existing services provides the potential for immediate post-study implementation. While the impacts of telephone-based lifestyle programmes have been tested in a number of settings, there are few studies which evaluate the effectiveness and acceptability of telephone support in achieving healthy gestational weight gain in association with routine antenatal care.

**Trial registration:**

ACTRN12615000397516 (Registration date: 26 June 2014, retrospectively registered).

**Electronic supplementary material:**

The online version of this article (doi:10.1186/s12913-016-1704-z) contains supplementary material, which is available to authorized users.

## Background

Excessive gestational weight gain (EGWG) is associated with poor maternal and infant health outcomes, including an increased risk for gestational hypertension, gestational diabetes, caesarean section, low apgar scores and infants who are born large for gestational age [1–4]. There is also an increased likelihood of postpartum obesity in both mothers [2] and their children [5], which in turn leads to an increased risk of chronic disease later in life [6]. Risk factors for EGWG include a high pre-pregnancy BMI, with some studies showing that women who are overweight or obese prior to pregnancy are 2–6 times more likely than women with a normal BMI to be at risk of EGWG [7, 8]. EGWG in women of all pre-pregnancy BMIs can lead to a progressive weight gain which is retained over a woman’s reproductive years [9].

The Institute of Medicine (IOM) gestational weight guidelines [10] were updated in 2009 and are the most frequently utilised internationally. The guidelines provide ranges of recommended weight gain for specific pre-pregnancy BMI categories, based on the least risk of adverse perinatal outcomes [11]. It has been suggested that the gestational weight gain for most women in reality exceeds the IOM recommendations [11, 12], and in Australia, the prevalence of EGWG has been reported as being between 38 and 67 % [13, 14]. The first national guidelines for antenatal care in Australia were published in August 2013, recommending that clinicians give women advice about appropriate weight gain during pregnancy in relation to their pre-pregnancy BMI [15].

Diet and exercise are modifiable risk factors for EGWG, and a number of interventions have been trialled to reduce EGWG by changing dietary and physical activity behaviours. Evidence to date however is mixed with some interventions either not resulting in a significant decrease in EGWG or only proving effective in certain groups, such as women with a normal pre-pregnancy BMI [11, 16, 17]. Changes in diet and physical activity can result in lower weight gain but what is not known is the mechanism by which this is achieved.

Most reported interventions are resource-intensive in terms of face to face specialist professional support and therefore unsustainable in the long term. Simple strategies such as giving women accurate advice regarding a target gestational weight gain [18], and encouraging women to self-weigh [19] appear to be effective in some groups. As in the non-pregnant population, intensive initiatives that provide regular reminders appear to produce the most effective results [20]. It seems that these do not have to be delivered directly by clinicians; Soltani et al. [21] utilised text messaging to deliver simple regular reminders with positive results, although the study numbers were too small for statistical analysis.

A recent study by Dodd et al. [22] employing a combined telephone and face to face intervention for overweight and obese pregnant women did not find any improvements in maternal and birth outcomes compared with standard care, but their study sample was skewed towards women from high socio-economic backgrounds who are more likely to have a higher baseline for health behaviours than the general population [23]. The study also did not provide women with a target gestational weight gain or evaluate the acceptability of the service.

The process of telephone-based health coaching, delivered by qualified dietitians and exercise physiologists unrelated to the client’s clinical care, is a relatively new concept for maternity care providers, although well established for patients with chronic disease [24]. It is designed to support clients through regular contact to achieve a healthier lifestyle through the use of behaviour change theory, thereby also supporting the work of time-poor clinicians. A free telephone-based health coaching, the Get Healthy Information and Coaching Service (GHS), has been available to all adults over 18 years of age in New South Wales (NSW), Australia since 2009. People using this service can opt to receive information only or enrol in a six month coaching program. The program consists of 10 individually tailored calls from university qualified coaches, aimed at making sustained improvements in healthy eating, physical activity and achieving or maintaining a healthy weight. Extensive evidence exists for the effectiveness of telephone-based lifestyle programs and evaluation of the GHS itself shows that participants who complete the 6 month coaching program lose an average of 3.9 kgs and reduce their waist circumference by 5.0 cms. [25] The GHS has a considerable proportion of participants who are female (73 %) and reside outside of major cities (40 %) as well as being from lower socio-economic backgrounds [26].

### The NSW Get Healthy in Pregnancy Service (GHiP)

A telephone-based service for pregnant women of New South Wales (NSW), Australia, Get Healthy in Pregnancy (GHiP), was developed in collaboration between the NSW Office of Preventive Health and NSW Kids and Families to support women to achieve appropriate gestational weight gain through health coaching. GHiP was developed as an enhancement to the GHS. Development of GHiP has been informed by evaluations of other interventions aimed at reducing EGWG with the input of an Expert Advisory Panel including midwives, obstetricians, dietitians and antenatal educators from across NSW. Pregnant women have suggested in a qualitative study in the UK that they would prefer a healthy eating service that is integrated into routine care and provides information early in their pregnancy [27]. Two potential models for the GHIP integrated with hospital antenatal care have been developed and will be compared as the two arms in this study:*Information only* – introduction of gestational weight gain recommendations by midwife at their initial hospital antenatal appointment, evidence-based factsheets and an information booklet on healthy eating, exercise and weight gain during pregnancy in line with Australian guidelines [28–30], and a single health coaching call; and*Health coaching* – introduction of gestational weight gain recommendations by midwife at their initial hospital antenatal appointment, the same factsheets and information booklet as the information only group, plus a journey booklet to record progress and up to 10 health coaching calls (8 during pregnancy, 2 post pregnancy).

Both service models commence between 12 and 22 weeks gestation. Participants receiving health coaching are offered coaching calls up until 36 weeks gestation and receive two coaching calls at 10 and 14 weeks post-delivery.

## Methods/Design

### Aims and objectives

This study will compare the effectiveness of a telephone-based health coaching program versus provision of information alone in supporting pregnant women to achieve appropriate gestational weight gain. Pregnant women will be stratified into pre-pregnancy healthy weight and overweight/obese groups. Given the evidence around issues related to excessive weight gain in pregnancy, a pure control group was not included in the study as it was considered inappropriate to not provide information that could be beneficial to maternal and neonatal health.

The hypothesis of the study is that, pregnant women enrolled in the coaching program will be more likely to achieve a healthy gestational weight gain during pregnancy and better maintain their pre-pregnancy weight post pregnancy. Weight-gain that is above the IOM guidelines is considered excessive gestational weight-gain.

The primary objectives of the study are to:i)Compare the differences in gestational weight gain and weight retention at 12 months post birth of participants in the health coaching and information only armsii)Understand the acceptability and experiences of telephone-based coaching amongst pregnant women and antenatal service providers.

As secondary objectives, the study will:iii)Compare changes in diet (fruit, vegetable, fast food and sweetened drink intake)iv)Assess the predictors of service participation and retentionv)Explore service usage patterns such as length of calls and preferred timevi)Assess confidence to changevii)Provide recommendations for program improvement.

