### Sample size

A total of 710 women will be recruited; 177 and 532 pregnant women with a pre-pregnancy BMI of 18.5–24.9 kg/m^2^ (healthy range) and ≥25.0 kg/m^2^ (overweight or obese range) respectively. 248 women will be recruited across the three rural hospitals with 462 recruited at metropolitan hospitals. The higher numbers in metropolitan hospitals is to reflect the larger target population in these areas.

The sample size has been calculated using previous reports of weight gain during pregnancy [10, 13, 33] to detect a difference of 3 kgs in gestational weight gain between intervention and control groups at 80 % power. Attrition rates of 60 % in the coaching arm and 30 % in the information only arm are expected. These rates account for the up to 15 % of women, across both arms, who start the study and go on to develop conditions during pregnancy that exclude them from further participation [34] and, allows for the perception of participant burden in the coaching arm. The relatively high attrition rate is conservative compared with other population based programs.

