### Data analysis

#### Primary objectives

All quantitative data analysis will be based on intention to treat principles. Differences between the two study groups in self-reported weight change from pre-pregnancy weight to weight at 36 weeks gestation and 12 months post birth will be tested using the independent samples *t*-test. The proportions of pregnant women who achieve weight gain within the recommended range and those who return to their pre-pregnancy weight 12 months post birth will be analysed using the *X*^2^ test. The adjusted means of the BMI outcomes at 36 weeks gestation and follow up by BMI category will be compared with the pre pregnancy BMI.

Interview data will be analysed using the thematic analysis approach. The transcribed interviews will be coded by the researchers and if there is a disagreement in the classification of interview responses, the researchers will convene as a group to discuss the discrepancies and revise coding categories if needed. Once agreement is reached, themes and sub-themes will be extracted from the data. Data from the interviews will inform the provision of recommendations for program improvement.

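### The protocol does not settle on one primary outcome: four between-arm tests serve the primary objective, and only mean weight gain was sized

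*Protocol article*

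**What the plan says.** **Aims and objectives.** The first primary objective is to "Compare the differences in gestational weight gain and weight retention at 12 months post birth" across the two arms. It holds two quantities, and neither is said to decide the trial. The hypothesis is that women in coaching will be "more likely to achieve a healthy gestational weight gain during pregnancy and better maintain their pre-pregnancy weight post pregnancy". The second primary objective, on acceptability, is qualitative and plays no part in this point.

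**Data analysis, Primary objectives.** The t-test is applied to "Differences between the two study groups in self-reported weight change from pre-pregnancy weight to weight at 36 weeks gestation and 12 months post birth". The chi-square test is applied to "The proportions of pregnant women who achieve weight gain within the recommended range and those who return to their pre-pregnancy weight" at 12 months. A further comparison, "The adjusted means of the BMI outcomes at 36 weeks gestation and follow up by BMI category", is made against pre-pregnancy BMI. It is not counted here because it is not set out as a comparison of the two arms.

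**Sample size.** The 710 women are to be enough "to detect a difference of 3 kgs in gestational weight gain between intervention and control groups at 80 % power". No power is given for the 12-month mean or for either proportion.

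**The concern.** The objective, the hypothesis, the tests and the sample size should lead to the same outcome, and here they do not. The objective points to two quantities, the hypothesis opens with a likelihood of success, the analysis offers two scales for each quantity, and the sample size concerns one mean.

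The scale matters. A lower mean gain can come from fewer women above the recommended range or from more women below it. The t-test and the chi-square test on the same weights can therefore disagree, and the text does not say which would then answer the primary objective. The rank of 12-month retention is open in the same way.

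At stake is what may be reported as meeting the primary objective. If one favourable result among four were enough, the false-positive rate would exceed the nominal level, and the result could rest on a comparison with no stated power.

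**Working it through.** **1. Which outcome each section points to**

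| Section | Quantity | Scale |
|---|---|---|
| Aims and objectives, objective (i) | gain and 12-month retention | not given |
| Aims and objectives, hypothesis, first half | gain | proportion |
| Aims and objectives, hypothesis, second half | weight after pregnancy | not given |
| Data analysis, Primary objectives | both | mean and proportion for each |
| Sample size | gain only | mean, 3 kg |

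Two quantities on two scales make four between-arm tests.

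**2. The plan's own figure**

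The 710 can be neither reproduced nor refuted, because the SD, the alpha level and any design effect are not given. Assume 1:1 recruitment, which is also not stated, and apply the stated attrition of 60% and 30%:

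- coaching: 355 × 0.4 = 142
- information only: 355 × 0.7 = 248.5

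At an assumed two-sided 5% level and 80% power, the SD that 710 implies is 3 / [(1.960 + 0.842) × √(1/142 + 1/248.5)] ≈ 10.2 kg. With an SD of 5, 6 or 8 kg, the same formula needs about 172, 248 or 440 women. The calculation covers mean gain only.

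**3. False-positive rate if any one of the four tests suffices**

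Independent tests:

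- either direction: 1 − 0.95⁴ = 18.5%
- in favour of coaching: 1 − 0.975⁴ = 9.6%, against 2.5%

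The tests are correlated, so this overstates the rate. A simulation with no true difference was run on 142 v 248 women, with 20,000 trials per row. Its assumptions are SD 6 kg for both weight changes, mean gain 13 kg, mean retention 2 kg, 25% of women of healthy weight, and illustrative target ranges (11.5–16 kg for healthy weight, 6–11.5 kg otherwise). Each test alone ran at 4.8–5.5%.

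| Correlation of gain and retention | Any of four, either direction | Any of four, favouring coaching | Two t-tests only, either direction |
|---|---|---|---|
| 0 | 16.5% | 8.7% | 9.7% |
| 0.3 | 16.8% | 8.3% | 10.1% |
| 0.5 | 16.0% | 7.9% | 9.2% |
| 0.7 | 15.4% | 8.0% | 8.6% |
| 0.9 | 14.1% | 7.2% | 7.2% |

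To check dependence on these assumptions, four correlated normal statistics were drawn over a grid: correlation 0.4 to 0.8 between the two tests of one quantity, and 0 to 0.7 between quantities. The rates were 13.3–17.8% in either direction and 6.6–9.1% in favour of coaching.

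**4. If both quantities had to succeed**

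Having two quantities would then add no inflation, and only the choice of scale within each would remain. Where one quantity truly differs and the other does not, the error is at most that of two tests on the null quantity: 1 − 0.95² = 9.75% in either direction if they were independent, and less because they are correlated. Where neither differs, it is far smaller.

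**The case against.** Four points can be made for the plan.

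- **The lead quantity can be recovered.** The study aim, the order within the objective and the sample size all put gestational weight gain first. This stands. What stays open is narrower: the scale on which gain is judged, and the rank of 12-month retention.
- **The hypothesis is conjunctive.** Read as a joint requirement, it removes most of the inflation. This stands as a possible reading, but the analysis section sets no joint rule, and each part would still have two candidate tests.
- **Order and adjustment belong in an analysis plan.** Agreed: the absence of a multiplicity method from an article is not the point. The article does, however, fix the objective, hypothesis, tests and sample-size basis itself, and these disagree.
- **Within-range gain is closer to the stated aim than mean gain.** This is fair. It is an argument for choosing deliberately, but only mean gain has been sized.

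A reader might infer that the plan carries about three times the nominal chance of a false claim of benefit. The document does not support that as a flat statement. It gives neither an alpha level nor a rule that any one of four tests suffices. The 14–17% also counts results against coaching. Nor can one infer that the deciding outcome will be picked after the data are seen: the article cites a trial registration, and neither that record nor a separate analysis plan is at hand.

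**Conclusion.** The point holds in limited form. The aims, the sample size and the primary analysis do not agree on one primary outcome and scale, and four tests share that role with only mean gain sized.

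The inflation is conditional. With a two-sided 5% level, 1:1 recruitment and any one of four tests counted as success, it is about 14–17% in either direction, or about 7–9% against 2.5% for a false finding in favour of coaching. If only the two t-tests counted, it is about 7–10% in either direction, roughly 1.5 to 2 times nominal. A joint rule would bring it much lower. The multiple near three therefore belongs to the least favourable reading and is not a property of the plan as written. These figures cover multiplicity only and leave hospital clustering aside.

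The plan should be changed on this point, because the ambiguity lies in the protocol's own text and is easily removed.

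**What to change.** In Aims and objectives and in the primary analysis text, do one of the following before outcome data are seen:

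- **Single primary outcome.** Name mean weight gain from pre-pregnancy to 36 weeks, the only sized quantity. Make within-range gain, 12-month weight retention and return to pre-pregnancy weight secondary.
- **Fixed order.** Test mean gain, then the within-range proportion, then 12-month weight change, then return to pre-pregnancy weight, each at the full level, stopping at the first non-significant result.

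Reword the hypothesis to match.

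As far as multiplicity is concerned, either option returns the error rate to the nominal level, keeps the planned 80% power for mean gain and needs no more women. Bonferroni over four tests (0.0125 each) would be dearer. Power for 3 kg would fall to Φ(2.802 − 2.498) ≈ 62%. Restoring 80% would take (2.498 + 0.842)² / (1.960 + 0.842)² ≈ 1.42 times the sample, about 1,009 women.

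The cost is that a result found only on a secondary outcome, or after the order has stopped, could no longer be claimed as the primary result. The registered outcomes may also need updating.

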### Study design

This study employs a pragmatic stratified cluster randomised design [31] with stratification by healthy weight and overweight/obese pre pregnancy BMI.

Pregnant women in the study will be allocated to either the information only or health coaching group based on the hospital where they present for antenatal care (Fig. 1). This design was selected to obtain results that can be generalised with high external validity and utility in the real world setting. In this study, the trial environment and processes will be as close as possible to how the program would be rolled out if effective. A range of hospitals in both metropolitan and rural settings, of different sizes and maternity service delivery levels have been chosen to test the scalability of the intervention across the state.

**Fig. 1 Fig1:**
[figure not shown]
Study flowchart

Randomisation of hospitals, stratified by metropolitan and rural regions, will be undertaken using Microsoft Excel 2010© randomisation generator. Two rural hospitals were combined into one unit for randomisation because they are in the same Local Health District and their aggregated total number of births in 2012 was similar to the total of the other rural hospital in the study. Face-to-face training will be provided, by members of the research team, to the midwives and medical officers at each site to describe the study and the program. The hospitals will develop their own processes to integrate the GHiP referral into the first antenatal appointment for pregnant women. As part of this process, hospitals in both arms will be required to include initial discussion on the importance of healthy gestational weight gain, the setting of a target weight-gain range for the woman’s pregnancy (as per IOM recommendations), screening of the woman for exclusion criteria and recruitment of women following consent.

Health coaches (primarily dieticians and exercise physiologists) delivering GHiP will be provided with a day’s face-to-face training by clinical experts in dietetics and maternity care, in addition to their usual training. A list of online resources to support the pregnant women will also be available to all health coaches. The clinical experts will also be available for further consultation as required.

